#### Intervention description {11a}

All the recruited patients will receive general anesthesia. Cefamandole will be administered intravenously 30 min before and after surgery. Low molecular weight heparin for thromboprophylaxis will be administered subcutaneously 8 h postoperatively and then once daily for 2 weeks. Preoperative oral doses of 400 mg celecoxib will be administered from day 1 before surgery. Postoperatively, all the patients will receive 40 mg of parecoxib sodium twice intravenously until postoperative day (POD) 3, followed by oral doses of 200 mg celecoxib every 12 h for 4 weeks. The chief investigator (DG) will perform all the operations. A Depuy Attune PS prosthesis (Attune ®; DePuy Synthes, Warsaw, IN) will be inserted via a standard medial parapatellar approach in all patients.

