#### Provisions for post-trial care {30}

As a routine follow-up plan, participants are advised for clinic follow-up visits at 2 weeks, 4 weeks, 8 weeks, and 3 months; the investigators (CZ and LZ) will contact the participants for routine clinical follow-up as post-trial care. Previous studies on the intravenous use of corticosteroids have shown that postoperative blood glucose rise, gastrointestinal ulcers, and poor wound healing could occur. In this study, the topical use of corticosteroids may have similar risks during the trial. These adverse events are included in the common adverse events of TKA and will be covered by the government health care insurance.

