#### Adverse event

Adverse events during the trial include serious adverse events (SAEs) and common adverse events. SAE in TKA is defined to cause serious results that required surgical treatment or intensive treatment during the first 3 months following TKA [24, 25]. Common adverse events are minor operation-related complications requiring additional care, but little threat to the patients’ life [25–28]. A brief description of adverse events is summarized in Supplementary Table 1. It should be noted that all hospital adverse events in each patient will be collected. The total occurrence rate of common adverse events will be analyzed and defined as the presence (yes) or not (no) of any event within the entire trial. For example, if a patient experienced postoperative anemia, nausea, and hypertension during hospitalization, he or she will be counted for a “yes” only once. Moreover, if a patient only experienced vomiting one time, he or she will likewise be counted for a “yes.” This will also be applied to the computation and analysis of SAE.

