#### Adverse event reporting and harms {22}

All SAEs will be recorded in the medical records and case report forms, including the onset date, complete description of the event, severity, duration, action taken, and outcome. The chief investigator will complete the SAE form, and the form will be emailed to the ethics committee of The Second Affiliated Hospital within five working days of awareness of the event. The chief investigator will respond to any SAE queries raised by the ethics committee as soon as possible. All common adverse events will be recorded on the case report forms.

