## Discussion

In TKA, an enhanced recovery strategy warrants improved patient comfort during hospital stay and accelerated discharge. Consequently, measures to control pain and accelerate rehabilitation are important. Although the MCPI technique has been proven to be a safe and cost-effective measure, the gold standard for drug combinations has not yet been established. Corticosteroid addition to MCPI is believed to be a key component owing to its local anti-inflammatory effects and ability to reduce the local stress response following surgery. However, there is conflicting evidence regarding its benefits for pain control following TKA. Christensen et al. [18] conducted a randomized controlled trial that compared patients who had MCPI with 40 mg of methylprednisolone or without corticosteroids, and the only significant result was a decreased LOS in the steroid cohort (2.6 vs. 3.5 days). There was no difference in pain scores, ROM, or Knee Society scores at any time point. Chia et al. [17] compared patients who had an MCPI containing high- or low-dose corticosteroid with patients’ MCPI without corticosteroid, and they were unable to find any significant clinical effect on postoperative ROM advantage and pain relief at the two different dosages. In contrast, Seah et al. [16], who used 40 mg of triamcinolone acetate, found a significant reduction in the early postoperative pain scores and lasting increase in the ROM in the steroid group. Wang et al. [10] found that addition of corticosteroids to an analgesic cocktail could prolong the analgesic effects of local anesthetics, reduce inflammation, slightly improve immediate postoperative pain relief, and accelerate recovery in the first 24 h following TKA. They concluded that the additional analgesic effects of corticosteroids were mild and transient, and prospective studies are still needed to determine the best cocktail of periarticular infiltration analgesia. A meta-analysis by Chai et al. [29] demonstrated that cocktail analgesia containing corticosteroid periarticular injection did not contribute to pain relief within 12 h postoperatively; however, from 24 to 72 h, it significantly decreased the pain score at rest and reduced total rescue opioids. A recent meta-analysis by Li et al. [30] demonstrated that adding corticosteroids to multimodal cocktail periarticular injection can relieve the POD 1, POD 2, and POD 3 pain intensity at rest following TKA, with no significant difference in the VAS score at the operation night, POD 4, POD 5, POD 7, and 2 weeks following the operation. Owing to these conflicting results, we plan to design a three-arm, double-blinded randomized controlled trial containing a high or normal dose of corticosteroid MCPI and a noncorticosteroid MCPI to assess their effectiveness in postoperative pain relief, functional improvement, rescue analgesia, and side effects. This study will also provide clinical evidence on the effect of high-dose corticosteroid adjuvant to MCPI on prolonged pain control and better recovery following TKA.

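### The window for common adverse events is stated inconsistently (hospital events versus the entire trial), so non-serious events after discharge may be scored as absent

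*Protocol article*

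**What the plan says.** The Adverse event section makes three statements about common adverse events.

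- **Collection:** "It should be noted that all hospital adverse events in each patient will be collected".
- **Analysis:** the total occurrence rate is "defined as the presence (yes) or not (no) of any event within the entire trial".
- **Counting example:** "if a patient experienced postoperative anemia, nausea, and hypertension during hospitalization, he or she will be counted for a “yes” only once".

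A second example, a single episode of vomiting, has no setting attached.

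Serious adverse events (SAEs) are defined in the same section as those with serious results that "required surgical treatment or intensive treatment during the first 3 months following TKA". The yes/no counting rule applies to them too.

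Elsewhere:

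- Adverse event reporting and harms {22} states: "All common adverse events will be recorded on the case report forms". No period is given.
- Trial design {8} sets a 4-week follow-up. The last outcome assessments are at day 30.
- Provisions for post-trial care {30} warns, from studies of intravenous corticosteroids, that "postoperative blood glucose rise, gastrointestinal ulcers, and poor wound healing could occur". It places these risks among the common adverse events.

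**The concern.** The rule for collecting common events and the endpoint built from them use different windows. The endpoint is yes/no per patient, so an event that nobody asks about becomes a 'no' and not a missing value. Neither multiple imputation nor last observation carried forward would repair that.

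This matters because side effects are a stated aim in the Abstract and Discussion, and two of the three named corticosteroid risks, ulcer and poor wound healing, can appear after a patient has gone home. The third, a glucose rise, has its own scheduled blood tests to day 30, so it is less exposed. Background drug exposure also lasts well into the follow-up: after parecoxib the plan has celecoxib, "followed by oral doses of 200 mg celecoxib every 12 h for 4 weeks", and low molecular weight heparin runs for 2 weeks.

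A window that ends at discharge would also depend on length of stay, which is observed after randomization and could be affected by treatment.

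**Working it through.** The plan states no figure for the adverse event window, so there is nothing to reproduce. The check is mainly a comparison of the text.

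**1. Windows as stated**

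| Section | Events | Period |
|---|---|---|
| Adverse event, collection sentence | hospital events | no end given; 'hospital' undefined |
| Adverse event, first example | common events | hospital stay |
| Adverse event, endpoint | common events | whole trial |
| Adverse event, SAE definition | serious events | 3 months |
| Reporting and harms {22} | all common events | none given |
| Trial design {8} | trial follow-up | 4 weeks |

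The collection and endpoint rows agree only if 'hospital' includes events learned of at outpatient visits. The section does not say so, and the first example points to the inpatient stay. The whole-trial period is itself unclear for serious events, because a 4-week follow-up does not reach 3 months.

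**2. Which events are exposed**

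A late event that meets the SAE definition has its own 3-month window. A late event that does not, such as delayed wound healing needing only additional care, is a common event and falls in the gap. It changes the composite only in a patient with no earlier common event. In other patients the composite is already 'yes', and the late event would be missing only from any tabulation by type.

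**3. Illustration of size**

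Assumptions not in the protocol: collection stops at discharge on day L; stays of 5, 7 or 14 days; a 30-day event risk r of 5% to 20%; constant hazard.

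- Share of the window covered = L/30: 5/30 = 17%, 7/30 = 23%, 14/30 = 47%.
- Share of patients with an event who are captured = [1 − (1 − r)^(L/30)] / r.
  - L = 7: 0.0119/0.05 = 24% at r = 5%; 0.0507/0.20 = 25% at r = 20%.
  - L = 14: 0.0237/0.05 = 47% at r = 5%; 0.0989/0.20 = 49% at r = 20%.

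Constant hazard is only a convenience. Early events such as nausea would be captured more fully than this, and late wound or ulcer events less fully.

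**The case against.** The best defence is that this is loose wording and not a restriction. The collection sentence does not say 'only', and nothing in the article says that collection ends at discharge. The section concerns events during the trial, the reporting section carries no hospital limit, and clinic contacts are planned at 2, 4 and 8 weeks and 3 months. Severe late complications are covered by the SAE definition. The visit schedule (Figure 2) and the event list (Supplementary Table 1) are not shown and may settle the timing.

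Most of this stands, and it rules out two stronger readings that a reader might infer.

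- **That post-discharge events are missed.** The documents do not establish this. Nor can it be said that days 14 and 30 lack an adverse event review: the outcome paragraphs mention none, but the schedule is not available to check.
- **That the steroid arms get a shorter window and so look safer.** This needs both a cut-off at discharge and a difference in stay between arms. The only support for the second is one trial cited in the Discussion, of a different corticosteroid, with stays of 2.6 versus 3.5 days. Those stays fit poorly with intravenous parecoxib until postoperative day 3 and walking, circumference and blood measurements on day 5. They should not be used as a magnitude here.

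The defence does not remove the mismatch. The reporting section says where common events are written down, not for how long or at which contacts they are sought. The clinic visits are presented as retention and routine post-trial care, without mention of asking about events.

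**Conclusion.** The point holds as an inconsistency to be reconciled. The article gives no single window for common adverse events, and staff who followed the collection sentence literally would under-record non-serious events after discharge, including two of the corticosteroid risks that the protocol names. An arm-dependent window is possible but conditional on a difference in length of stay, which the protocol neither assumes nor lists as an outcome.

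The size cannot be derived from the documents. The 17% to 47% coverage shows only that the restrictive reading would leave more than half of a 30-day window unobserved for stays of up to 14 days. Confidence is moderate, because the schedule figure and the supplementary table could resolve the question of timing.

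**What to change.** Reconcile the Adverse event section, Trial design {8} and Adverse event reporting and harms {22}.

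1. Replace the collection sentence with wording such as: *all common adverse events from injection to day 30, in or out of hospital, in all arms*.
2. At the existing day 14 and day 30 assessments, have the blinded assessors complete a short fixed checklist with onset dates, covering wound healing or infection, gastrointestinal ulcer or bleeding, readmission and other events.
3. Compare the arms over that common window.
4. State separately how serious events are followed to 3 months when the trial follow-up is 4 weeks, for example through the clinic contacts already planned. The day 30 limit should not be applied to serious events.

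The cost is one case report form page and a few minutes at each of two assessments that already take place. Recorded event rates will be higher, which should be expected when comparing with studies that count inpatient events only. Recruitment began in October 2020, so participants already past day 30 will lack the checklist, and the report should say how their events were ascertained.

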### Statistical methods

#### Statistical methods for primary and secondary outcomes {20a}

Perioperative outcomes will be summarized using the mean ± SD for continuous variables and the ratio for categorical variables. All statistical analyses will be conducted using the SPSS software (version 13.0. for Windows; SPSS, Inc., Chicago, USA). For continuous variables, the Kolmogorov–Smirnov test will be used to detect the normality of distribution. Analysis of variance (ANOVA) will be used to compare the differences among the three groups, and Dunnett’s *t* test will be conducted to compare the between-group differences. For categorical variables, the chi-square test will be conducted to compare the intragroup differences, and partitions of chi-square methods will be used to compare the between-group differences.

For repeatedly measured outcomes, multivariate analysis for repeated measures ANOVA test will be performed to compare the difference between the three groups, which contains the three intervention groups, time, and group-time interaction. Dunnett’s test will be applied for post hoc comparisons. When the group-time interaction showed a significant difference, a one-way repeated measures ANOVA was conducted to identify the difference in effect between the three intervention groups. The significance level will be set at *α*=0.05. Statistical analyses will be performed by an independent investigator.

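### Common adverse events are compared as any-event yes/no, and no by-arm comparison is stated for gastrointestinal ulcer or poor wound healing, which the protocol names as steroid risks

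*Protocol article*

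**What the plan says.** The section Adverse event gives the counting rule: "The total occurrence rate of common adverse events will be analyzed and defined as the presence (yes) or not (no) of any event", taken over the trial as a whole. Two examples follow. In the first, "if a patient experienced postoperative anemia, nausea, and hypertension during hospitalization, he or she will be counted for a “yes” only once". In the second, "if a patient only experienced vomiting one time, he or she will likewise be counted for a “yes". The rule carries over to serious events: "This will also be applied to the computation and analysis of SAE". Serious events are those needing surgical or intensive treatment in the first three months; common events are minor complications.

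Provisions for post-trial care {30} says that, with intravenous corticosteroids, "postoperative blood glucose rise, gastrointestinal ulcers, and poor wound healing could occur". It adds that local use may carry similar risks and places these events among the common adverse events of knee arthroplasty.

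For categorical outcomes, Statistical methods {20a} specifies a chi-square test, after which "partitions of chi-square methods will be used to compare the between-group differences". Blood glucose is listed under Other outcomes for analysis on postoperative days 2, 5, 14 and 30. Adverse event reporting and harms {22} has every common adverse event entered on the case report form.

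**The concern.** Group H receives three times the betamethasone of group N (21 mg against 7 mg), and side effects are among the stated aims. The protocol identifies harms that could follow from the steroid, then puts two of them, ulcer and poor wound healing, into a yes/no variable that any routine post-surgical event can turn to yes. A patient already counted for anaemia or nausea cannot be counted again for a wound problem, so an excess of wound problems in group H shows only among patients who had no other event.

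The risk is one of interpretation. A flat any-event rate could be reported as showing no safety cost at the high dose, when the comparison had little ability to show a steroid-specific excess.

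**Working it through.** **Inputs from the protocol article.** 1:1:1 allocation, 78 per group, α = 0.05, chi-square test for categorical outcomes. The only stated sample-size figure concerns pain. A one-way ANOVA with means 0, 0.4 and 0.8 and SD 1.5 gives 69 per group (power 0.8015), which reproduces it. Inflating for 10% dropout gives 69/0.9 = 76.7, so 77 against the stated 78, a trivial difference. No adverse-event rate or power is given.

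**Assumptions.** Let s be the risk of a pooled steroid-event category (ulcer or wound-healing problem) and b the background risk of any other common event. Take b as equal across arms and independent of s. Then:

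- composite risk: p = 1 − (1 − b)(1 − s)
- H−C difference in the composite: (1 − b)(s_H − s_C)
- noncentrality of the three-arm chi-square: λ = n Σ(p_i − p̄)² / [p̄(1 − p̄)], 2 df, critical value 5.991

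**Direct comparison, s = 5/10/20% (C/N/H), n = 78.** p̄ = 0.1167 and Σ(p_i − p̄)² = 0.01167, so λ = 78 × 0.01167 / (0.1167 × 0.8833) = 8.83. Power is 0.76.

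**Same harm inside the composite.**

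| Background b | Composite C / N / H | H−C difference | λ | Power |
|---|---|---|---|---|
| 10% | 14.5 / 19.0 / 28.0% | 13.5 points | 4.52 | 0.46 |
| 30% | 33.5 / 37.0 / 44.0% | 10.5 points | 1.89 | 0.22 |
| 50% | 52.5 / 55.0 / 60.0% | 7.5 points | 0.92 | 0.13 |
| 70% | 71.5 / 73.0 / 76.0% | 4.5 points | 0.42 | 0.08 |

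The true difference is 15 points throughout. With 69 per arm the direct power is 0.71, and the four composite values are 0.42, 0.19, 0.12 and 0.08. For H against C alone at 78 per arm, power is 0.82 directly and 0.54, 0.27, 0.15 and 0.09 at the same backgrounds.

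**Smaller harm.** At 3/6/12%, direct power is about 0.5, against 0.22, 0.11, 0.08 and 0.06 in the composite. At 2/4/8%, nearer to what one event type might show, direct power is only about 0.35 (0.33 by simulation).

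**If the background also moves.** The Background section links nausea and vomiting to the stress response that the steroid is meant to reduce. Suppose b is 50/45/40% while s is 5/10/20%. The composite is then 1 − 0.50 × 0.95 = 52.5%, 1 − 0.55 × 0.90 = 50.5% and 1 − 0.60 × 0.80 = 52.0%. It is almost level (power 0.055) although the specific harm has quadrupled.

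**The case against.** Several points on the other side stand.

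- **Glucose.** A reader might infer that none of the three named harms has its own comparison. That is not so: blood glucose is an objective and is analysed separately over time.
- **Serious events.** A reader might also infer that every ulcer or wound event is mixed with nausea. Events serious enough to need surgical or intensive treatment go to a separate yes/no analysis. That too is an undifferentiated composite, but not one filled with minor events.
- **Exclusivity.** The article does not say the any-event rate is the only analysis. That reading rests on no other being stated. Supplementary Table 1 is not shown, event-level data will exist, and by-type tables are often left to an analysis plan. Counting each patient once is also a standard way to define an overall rate.
- **Size.** The rates are assumed, and the loss is partial when the background is low. The 0.76 belongs to a pooled category; single events would be rarer, the more so because a history of gastric ulcer is an exclusion. No passage sets a safety decision rule on the composite.

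What remains is that the article does not leave the matter blank. It fixes a rule for analysing common events, and that rule suits two of its own named risks poorly.

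**Conclusion.** The point holds for gastrointestinal ulcer and poor wound healing, not for blood glucose. The stated rule pools these two harms with routine events at equal weight, and no by-arm comparison of them is stated.

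Under the assumed 5/10/20%, independent background and 78 per arm, pooling lowers three-arm power from about 0.76 to between 0.46 (10% background) and 0.08 (70%). It would be too strong to say that a steroid signal is certain to be lost: that depends on a background rate the documents do not give. Nor would separate analysis guarantee detection, since power at 2/4/8% is only about 0.35. The gain lies mainly in estimating each named harm by dose and in not over-reading a null composite. This is a cheap improvement, not a flaw that threatens the trial.

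**What to change.** Keep the any-event rate as a summary. Prespecify, before unblinding, wound-healing problems and gastrointestinal ulcers as events of interest, pooled and individually, counting both common and serious events. Report counts by arm with H−C and N−C risk differences and 95% confidence intervals, using exact methods where counts are small. Read them together with the existing glucose analysis; no added glucose cut-off is needed. State that a non-significant composite will not be taken as evidence of no steroid harm.

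The cost is a short addition to the analysis text and one table, from data already on the case report forms. Treatment, visits and sample size are unchanged. The downside is a few more comparisons, which is acceptable if they are presented as estimates with intervals and not as further significance tests.

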#### Participant timeline {13}

Figure 2 shows the time schedule of enrollment, visits for participants, intervention, and assessments.

**Fig. 2 Fig2:**
[figure not shown]
Schedule of study procedures

#### Sample size {14}

The calculation of the sample size was based on previous studies. Ikeuchi et al. [13] reported that the POD 3 VAS scores were 27 ± 16 mm in the steroid group and 43 ± 18 mm in the control group. Kwon et al. [4] reported that POD 3 VAS scores were 35 mm in the steroid group and 41 mm in the control group. We assumed that the mean difference in the VAS score between the high-dose betamethasone group and control group was 0.8, and the mean difference between the normal-dose betamethasone group and control group was 0.4. An estimated standard deviation (SD) of 1.5, significance level (*α*) of 0.05, and power of test (*β*) of 0.8000 will be adopted. Based on the former data, the sample size was calculated as 69 participants per group. Assuming a dropout rate of 10%, the final sample size will be 78 participants per group, and 234 participants will be required for the three groups.

